
#### eTAU

Individuals in eTAU will receive an eCAP^TM^ for their foundational BD medication. This, in itself, may improve medication adherence behaviors [32]. The eTAU participants will also receive monthly automated text messages to refill medications and fill their eCAP^TM^ as well as the same brief general adherence promotion messages received by the CAE group for the duration of the study.

### Engagement and retention

As this is a group of participants who may be particularly difficult to engage and retain in the study, there will be a number of measures taken to optimize retention. These include scheduling visits at maximally convenient times for participants, allowing for frequent breaks as needed during the procedures, hiring and training staff that will be flexible and attentive to the individual’s needs and frequent opportunities for questions and feedback. Those in the CAE group will receive items to support the adherence modules such as a pill-minder, water bottle with study logo, etc. of minimal monetary value but that will be perceived as a personal connection. Should there be challenges in meeting enrollment goals, the study team will request input from the SAB in procedures and processes that might optimize enrollment. Finally, participants in all treatment groups will be compensated for research visits and interviews.

### Fidelity

Training of interventionists and measures to ensure fidelity to CAE will be similar to the procedures used in the CAE efficacy RCT for content/format for the duration of the study. To ensure generalizability of results to public-sector settings, each interventionist will devote only a portion of their overall time (0.25FTE) to the CAE intervention. After the initial training and throughout the study, CAE sessions will be recorded and 25% of the sessions (approximately 4 sessions every month) will be randomly selected and reviewed for fidelity by the senior interventionist or a fidelity rater trained by the senior interventionist. Fidelity assessment during the course of the study will evaluate CAE module-specific tasks on a Y/N or 0–10 scale. MET module fidelity assessment will include elements of the Motivational Interviewing Treatment Integrity (MITI) code [60]. Finally, CAE interventionists will participate in periodic teleconferences run by the senior interventionist to discuss implementation issues that may arise over time and in order to maintain standard approaches and minimize any potential variability.

### Assessments and outcomes

Table 2 shows the assessment measures and time-points, following the structure of a SPIRIT figure. Demographic and clinical variables measured at baseline will include age, gender, race/ethnicity, education, marital status, income, and health literacy [61]. Each participant will be assessed 6 times: at screening, baseline, 10 weeks, 6 months, 9 months, and 12 months. Data will be obtained from patient interviews. All assessments will be done by a rater trained to pre-established and documented reliability standards. It is expected that patient assessment will require approximately 120 min for the screening assessment and approximately 90 min for the follow-up assessments.

**Table 2 Tab2:**
[figure not shown]
Phase 2 measures and schedule of events [62]

^a^Service Engagement Scale and Ease of Access question will only be administered at V1

^b^only BPRS and MADRS will be administered at Screen

^c^Baseline should ideally be completed 2 weeks after screen, but no less than 1 week after screen to allow for sufficient time for eCAPs to be used

^d^Individuals who terminate study prematurely will have termination visit study assessments done at the time point that termination actually occurs

#### Primary outcome

##### Adherence

Adherence is defined as the percentage of days with doses missed with a higher value indicating worse adherence. Adherence will be evaluated in two separate but complementary ways, the self-reported TRQ for the past week and past month and the eCAP^TM^. The TRQ [40] is reliable for use in BD and shows a high correlation with lithium levels [63]. Adherence will be assessed for each evidence-based BD maintenance medication (lithium, anticonvulsant, antipsychotic) prescribed for at least 3 months. For individuals who are on more than one medication, an average TRQ will be calculated. While it is true that the literature on measurement of adherence, including the team’s own work in this area, notes limitations with all methods of adherence assessment, both self-report and automated pill caps appear valid and practical for use in BD studies [1, 32].

*eCAPs*^*TM*^
*(Information Mediary Corporation, Ottawa, ON, Canada)*: Electronic monitoring of pill container openings is an important method of measuring adherence. Pill bottles equipped with eCAPs^TM^ are capable of storing a 90-day supply of one medication. Once the eCAP^TM^ is activated by the Certiscan® Secure Reader, the eCAPs^TM^ record each time they are opened. The data are uploaded to the cloud remotely by scanning the eCAP^TM^ via an app on the participant’s personal smartphone or by using the Certiscan® Secure Reader. This provides a precise, objective assessment of the timing of each dose and the patient’s pattern of medication-taking behavior. Although many patients with BD take multiple maintenance BD medications, study staff will monitor the BD drug missed most often (index drug). If more than one drug is dosed at the same frequency, the BD drug most recently added to the regimen will be the index drug. As-needed or “prn” drugs will not be monitored. In previous work by this study team, the correlation between a single “index” BD drug and all BD drugs was 0.95 providing support for measuring one medication as proxy for medication adherence [64]. The method of choosing an index drug also limits participant burden. To ensure that the data collected represent pill-taking behavior as accurately as possible, patients will be instructed to dispense doses of their monitored medication only from the eCAP^TM^-equipped bottle, remove only one dose at a time, and remove a dose only at the time that they plan to swallow the medication.

While just assessing adherence behavior may temporarily increase adherence (e.g., the Hawthorne effect), it is expected that any potential impact on adherence behavior will wane over the 12-month follow-up. A recent large clinical trial demonstrated limited long-term adherence advantage for passive medication aids (e.g., 7-day pill organizer, pill cap displaying time since last dose), a category into which eCAP^TM^ would fall [65]. Experience with eCAP^TM^ in a pilot BD and hypertension adherence study [66] conducted by members of the study team yielded substantially less missing data using the eCAP^TM^ than the Medication Event Monitoring System (MEMS) [32]. Adding an extra financial incentive for bringing in the eCAP^TM^ or scanning it using the free eCAP^TM^ app on the participant’s phone ($10 per visit) optimizes use of automated pill monitoring. Notably, in the previously mentioned iTAB-CV R21 project using eCAPs^TM^, 31/38 participants (81.6%) brought their eCAP^TM^ to all 3 study visits over a 6-month period [66]. To optimize generalizability, individuals who use medisets or pill-minders to manage multiple medications will not be excluded from the study.

Only one medication will be tracked via eCAP^TM^. All other medications can remain in the pill-minder or other medication tracking device. The medication is placed in the eCAP^TM^ for the first time by the participant while the research assistant observes either in person or via videoconferencing. Participants will be trained on the use of eCAP^TM^ and will have the opportunity to practice opening the cap using a sample bottle if in person or have it demonstrated via videoconferencing.

#### CAE engagement targets

CAE targets patient-level adherence barriers and facilitators.

##### Health literacy

The Rapid Estimate of Adult Literacy in Medicine - Revised (REALM-R) [61] is an 11-item instrument designed to rapidly screen patients for potential health literacy problems. The measure is quick, taking only a minute or two, and identifies the grade level of the patient if they read below the ninth-grade level.

##### Adherence barriers

The Oxford Bipolar Knowledge Questionnaire (OBQ), a 40-item self-report will be used to assess knowledge of BD management. The OBQ uses a 3-point Likert scale to assess BD knowledge domains [67]. Routines will be assessed using the Self-Report Habit Index (SRHI), a 12-item self-report measure of habit strength, and will be administered regarding the habit of taking medication [68]. Provider communication will be assessed via the Communication Styles Scale, a patient-rated measure of the impact of physician communication style on medication beliefs and adherence behavior in depressed patients [69]. Alcohol use will be evaluated using The Alcohol Use Disorders Identification Test – Self-Report Version (AUDIT), a 10-item measure used to screen for excessive alcohol use developed by the World Health Organization [70]. Drug use will be evaluated using the Drug Abuse Screening Test (DAST-10), a 10-item abbreviated version of the original 28-item DAST created to assess drug-related problems in the past year [71]. Motivation to reduce the use of substances will be assessed using the 19-item Stages of Change Readiness and Treatment Eagerness Scale (SOCRATES 8A) [72].

##### Adherence facilitators

Engagement will be measured with the Service Engagement Scale (SES) [73, 74] for individuals with mental health conditions. The SES has 14 items that are rated on a 4-point scale ranging from 0 (not at all) to 3 (most of the time). The four subscales refer to availability, collaboration, help seeking, and treatment engagement. Staring and colleagues [75] used the SES to evaluate individuals with psychotic disorders who received adherence therapy. The SES has shown good psychometric properties [74]. Data will also be collected on attendance and reasons for missed appointments. Intervention acceptability will be evaluated with the 8-item satisfaction with service Client Satisfaction Questionnaire (CSQ-8) adapted to reference CAE [76]. CAE intervention’s perceived ease of access will be assessed via a single-item Likert scale.

#### Recovery outcomes

##### Functioning

Functional status will be evaluated using the Global Assessment of Functioning (GAF) [77]. The GAF is a 100-point single-item scale which measures global functioning of psychiatric patients and is widely utilized in clinical studies involving patients with serious mental illness [78].

##### BD symptoms

While symptoms in patients with chronic serious mental illness do not consistently correlate with adherence or change in adherence [36, 75], symptom assessment is still an important indicator of treatment outcomes and can be used to help identify sub-groups of individuals who may or may not benefit from behavioral interventions. BD symptoms will be assessed using the Brief Psychiatric Rating Scale (BPRS) [79], the Young Mania Rating Scale (YMRS) [80], and the Montgomery Asberg Depression Rating Scale (MADRS) [81]. Global psychopathology will be measured with the Clinical Global Impressions (CGI) [82], a widely used scale which evaluates illness severity on a 1 to 7 point continuum. Severity of illness ratings on the CGI have reported reliability scores ranging from 0.41 to 0.66.

#### Process and qualitative evaluations

Consistent with a Type 1 effectiveness hybrid design [30], quantitative program evaluation measures will map onto the RE-AIM framework [83] (Table 3) and qualitative evaluation will map onto the i-PARIHS framework (Table 1).

**Table 3 Tab3:** Quantitative program evaluation measures mapped onto the RE-AIM framework

RE-AIM domain	Evaluation measure
Reach	Patient enrollment, clinician referral counts
Effectiveness	Adherence, functional status
Adoption	Competency/fidelity among site mental health interventionists, CAE intervention engagement and attendance
Implementation	Intervention attendance, retention
Maintenance	Clinical site outpatient visits, no-show rate

##### Clinician referrals, health resource use

Prescribing providers will be encouraged to refer patients with BD that they believe are sub-optimally adherent and/or who would benefit from CAE. Referral sources and counts will be identified for all patients screened. To provide an indication of potential future maintenance/sustainability of the CAE intervention, resource use at both the clinical sites (outpatient visits, routine visit no-show rate) and off-site (emergency room visits and hospitalizations) will be evaluated. Self-reported resource use in the 6-month period prior to study enrollment and in the 12-month study period will be evaluated. To validate the self-report data, medical record documentation of service use will be evaluated in a randomly selected subset (20%) of the enrolled sample.

##### Patient qualitative evaluation

All participants in CAE will be asked to identify the degree to which the intervention met or did not meet their needs to help improve and maintain adherence. In addition, roadblocks as well as factors that can help use of CAE will be evaluated via qualitative interviews of patients who attended all or most (4 or 5) CAE sessions (*N*=10) and patients who attended 3 or fewer CAE sessions (*N*=10). The qualitative interview guide that was used to characterize participant perceptions in the CAE efficacy trial will be adapted for this effectiveness study. The interview guide will also be structured to align with i-PARIHS domains. Patient interviews will be conducted at the conclusion of the CAE modules and again at the 12-month follow-up point. To ensure a representative sample, we will attempt to balance by sex, race/ethnicity, and age and conduct the first set of patient interviews split equally in years 2 and 3 of the proposed project. All interviews will be recorded and transcribed.

##### Clinician, health system, SAB qualitative evaluation

At the conclusion of the modules, and again at the 12-month follow-up, prescribing clinicians (whether they referred an individual or not) will be queried regarding their perception of the effect of the intervention on patient adherence. In year 4, in order to optimize potential exposure to CAE in the clinic, interviews of a subset of providers representative of the mix of clinicians that provide care for patients with BD at the CMHC (*N*=10) will be conducted. All interviews will be recorded and transcribed.

## Data collection and management

Study data will be collected and managed using REDCap, a secure, web-based application designed to support data capture for research studies providing (1) an intuitive interface for validated data entry; (2) audit trails for tracking data manipulation and export procedures; (3) automated export procedures for seamless data downloads to common statistical packages; and (4) procedures for importing data from external sources [38]. Only study team members will be able to access the REDCap project which saves to servers in the CWRU Secure Research Environment. Data files, including analysis files, will be password protected to permit access and modification only by authorized persons. Participant names or similar potential identifiers (e.g., addresses, hospital record numbers) will not appear in any dataset.

Lists of potential participants will be saved within the secure server respective to the institution the patient is recruited from and will only be accessible by study staff, including CWRU research staff who have been research credentialed at both sites. The personal information will only be kept for as long as necessary (i.e., until the participant is enrolled or documented as a pre-screen failure). For those participants who cannot be contacted, refuse participation, or otherwise do not qualify for the study, only aggregate numbers will be retained to keep track of recruitment efforts. Careful attention will be given to confidentiality, which will be maintained using subject identification (ID) codes for enrolled participants. The list that links study ID codes with subject names and all forms bearing subject names and contact information will be stored in password-protected files on the respective institutions’ secure servers. Research files are not and will not be available to any unauthorized person.

As in the efficacy RCT, rigorous development of data collection forms and training of staff on the proper completion and checking of data collection forms will reduce errors at the point of collection. Additional data management practices before and after entry into the database will identify potential problems or outlying values and will catch other errors on data collection forms. Data management staff will be responsible for tracking forms entered and for performing routine auditing data checks. Analytic data sets will be prepared using SAS 9.2 or a similar statistical software package.

### Data analysis plan

For the primary intent-to-treat analyses (Aim 2), mixed effects longitudinal analysis of TRQ past week and past month over the 6 time periods will be conducted. The intention-to-treat sample will include all enrolled participants who complete baseline evaluation. A treatment variable will be included to indicate randomization to either CAE or eTAU. The lead trial statistician will be blinded for the analysis. Within the longitudinal model, significant interaction of the treatment variable with time indicates that the treatments have a different course of response. We will first fit models with time as a continuous covariate. Alternatively, we will also consider time period as a categorical variable. These interactions will be of primary interest. To account for possible imbalances across treatment groups and other sources of variation, explanatory variables such as sex and ethnicity and BD diagnosis type (I vs. II) will be considered for inclusion in the mixed models. Random effects will include a random intercept and possibly a random slope or other function of time as needed to suitably capture the within-person correlation structure. For TRQ, high success rates may lead to values concentrating on or close to the value zero in terms of percent medication missed, but there may be some persistent non-adherence as well, leading to non-normal data. With prior study data, we have taken the difference in subsequent TRQ scores from the baseline TRQ score to obtain resultant data that appear normally distributed. This is the approach we adopt for the power analysis below. As appropriate, we will also consider representing scores as binary outcomes, indicating whether or not an adherence threshold has been met (e.g., 80% adherent). We will thus consider generalized linear mixed models for binary outcomes (SAS PROC GLIMMIX), as well as fitting a longitudinal model on the difference values with baseline value adjustment. Graphical methods will be used extensively to examine distributions of residuals, identify potentially influential points, and guide data transformations to better approximate normality if warranted. Sensitivity analysis of results will be conducted by modeling a range of plausible correlation structures. Importantly, we will systematically assess the missing at random (MAR) assumption for mixed models. We will assess the sensitivity of the results through pattern mixture and selection model approaches that relax the missing at random assumptions [84].

We will study reasons for dropout and identify variables for possible inclusion in binary regression models of dropout by 10 weeks. Treatment differences in dropout models will be of interest. Additionally, we will compare corresponding TRQ and eCAP^TM^ adherence levels. Correlation between the measures will be estimated and Bland-Altman plots will be generated [85]. Secondary follow-up analyses at 9 and 12 months will also be compared in longitudinal analyses.

For Aim 3 and additional secondary analyses, GAF scores will be analyzed in a similar manner as in Aim 2. From previous experience, we expect GAF scores to approximately be normally distributed. Exploratory analysis will examine whether reductions in adherence barriers (e.g., BD knowledge, medication routines, communication, and substance) and increases in facilitators (patient satisfaction, ease of access, engagement) mediate the treatment effects on adherence. Further, secondary analyses will assess the mediation effects on functioning through adherence improvement. We will conduct simple mediation analyses, as well as multiple mediator models, using approaches described by Mackinnon and colleagues [86] and Preacher and Hayes [87]. Potential confounder variables will be included as covariates, such as age, sex, ethnicity, health literacy, BD type I vs. II, and substance use comorbidity. Bootstrapping methods will be used to assess indirect effects [87]. We will also consider, as needed, use of generalized linear models through a mediation formula approach [88, 89] to estimate the direct effect of the treatment and indirect effects through each mediator as well as through the set of mediators. Variable selection methods such as lasso will be used when multiple mediators are considered simultaneously to reduce redundancy. Moderators of treatment to be explored for each of the primary outcome models include covariates such as age, sex, ethnicity, health literacy, BD type I vs. II, and substance use comorbidity.

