### Power analysis

Sample size projections are based on computations from the Repeated Measures and Sample Size (RMASS) software [90] with inputs estimated from prior study data. For sample size requirement for Aim 2, we used past-week TRQ as an approximation of expected and longer-term maintenance adherence status, and we consider primary outcomes to be at 6 months. First, note that at 6-month follow-up, there was a 34.6% improvement in TRQ observed with the CAE pilot, compared to 25.5% in the prior control arm (EDU). The control comparator used in the effectiveness trial, eTAU, is less intensive, with no extra face-to-face sessions, in contrast with EDU. For the control arm in a previous BD RCT [91], a 7% improvement in self-reported adherence was reported. The average of these differences is around 18%. Also, to alleviate deviation from normality, we model difference values from baseline, adjusting for the baseline value as a covariate. We note that compound symmetry and autoregressive (AR(1)) covariance models led to similar model fits in terms of treatment effect *p*-values and model fit criteria. Finally, in the previous CAE R01 study, we observed approximately 20% attrition by 6 months. We thus believe it is conservative to assume the following: (1) There is a mean difference of 16% in improvement from baseline at 6 months between CAE and eTAU; (2) under an error correlation structure of compound symmetry, suppose a small within-subject correlation near 0.08 and an error variance of 504, as estimated value from the data; and (3) assume that attrition will be 30% by 6 months. For a two-sided test of the treatment by time interaction effect being equal to zero, with alpha = 0.025 and power = 0.80, the required total sample size is approximately 182 in total.

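### The primary Aim 2 slope test runs over all six assessments to 12 months, while the stated primary time point is 6 months, so months 6–12 can decide the primary result

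*Protocol article*

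**What the plan says.** All references are to the protocol article.

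- Data analysis plan, primary intent-to-treat analysis for Aim 2: "mixed effects longitudinal analysis of TRQ past week and past month over the 6 time periods will be conducted".
- Assessments and outcomes gives the only list of six: "Each participant will be assessed 6 times: at screening, baseline, 10 weeks, 6 months, 9 months, and 12 months".
- Form of time: "We will first fit models with time as a continuous covariate", followed by "Alternatively, we will also consider time period as a categorical variable". Of the treatment-by-time terms: "These interactions will be of primary interest".
- Power analysis: "we consider primary outcomes to be at 6 months". The sizing assumption is "There is a mean difference of 16% in improvement from baseline at 6 months between CAE and eTAU", with 30% attrition by the same point.
- Data analysis plan, later paragraph: "Secondary follow-up analyses at 9 and 12 months will also be compared in longitudinal analyses".

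The Primary outcome section gives no time point. Nothing in the article limits the primary model to 6 months or names a 6-month contrast from it.

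**The concern.** These statements do not define one test. If all six assessments enter a model with time as a straight line, the treatment-by-time coefficient is a single slope over about a year. The 9- and 12-month visits lie furthest from the centre of the time axis and so pull hardest on it. The trial was sized for something else: a difference reached at 6 months.

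Two trials with the same 6-month benefit could then reach opposite primary conclusions because of what happened afterwards. A trial with no 6-month benefit could be declared positive. Because the article supports both horizons, the choice could also be made after the data are seen.

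**Working it through.** **1. Which horizon was sized?** Inputs from Power analysis: difference 16, error variance 504, compound symmetry with correlation 0.08, 30% attrition by 6 months, two-sided alpha 0.025, power 0.80. The linear-contrast formula for repeated measures is

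N = 4(z₁₋α/₂ + z_power)² · c′S\*c / (c′d)²,

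where S\* is the covariance matrix with each element divided by the square root of the product of the two retentions. I read 504 as residual variance, so total variance is 504/0.92 = 547.8 and covariance 43.8.

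For three equally spaced points ending at 6 months, c = (−1, 0, 1), d = (0, 8, 16) and retention is 1, 0.85, 0.70:

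- c′S\*c = 547.8(1 + 1/0.70) − 2(43.8)/√0.70 = 1225.7, and c′d = 16
- (2.241 + 0.842)² = 9.505
- N = 4 × 9.505 × 1225.7/256 = **182.0**, the plan's figure.

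The actual spacing (0, 2.3, 6 months) gives 183.5. Six equally spaced points ending at 16 give 129.3, or 119.0 if 504 is total variance. Other readings of the 6-month design give 167.5 (504 as total variance) or 196.8–213.9 (simple inflation for dropout). The exact match corroborates a 6-month horizon but does not prove it.

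**2. What does the six-visit slope test respond to?** Generalised least squares, N = 190, alpha 0.025, total variance 504, correlation 0.08, times −0.5, 0, 2.3, 6, 9 and 12 months. Retention is 0.70 at 6 months (plan); 0.85 at 10 weeks and 0.65/0.60 at 9/12 months are assumptions. Information is summed over dropout patterns j, each with proportion p_j: I = Σ p_j X_j′S_j⁻¹X_j, and SE(slope) = √(4[I⁻¹]₂₂/N) = 0.324 per month. Power = Φ(slope/SE − 2.241) plus a negligible lower tail.

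| Difference between arms | Slope per month | Power, six visits |
|---|---|---|
| 16 by 10 weeks, kept | 1.376 | 0.98 |
| 16 by 10 weeks, 8 at 12 months | 0.831 | 0.63 |
| 16 by 10 weeks, 0 at 12 months | 0.287 | 0.09 |
| Linear to 16 at 6 months, kept | 1.516 | 0.99 |
| Linear to 16 at 6 months, 8 at 12 months | 0.972 | 0.78 |
| Linear to 16 at 6 months, 0 at 12 months | 0.427 | 0.18 |
| 0 through 6 months, 8 at 9, 16 at 12 | 1.089 | 0.87 |

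Example: 0.831/0.324 = 2.57, and Φ(2.57 − 2.24) = 0.63. In the first six rows the 6-month difference is 16 throughout. In the last it is zero, and a slope test on data through 6 months would reject at 0.025.

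**3. Sensitivity.** With total variance 504/0.92 the SE becomes 0.324 × √(1/0.92) = 0.338. The first three rows become 0.97, 0.59 and 0.08, and the last 0.84. On that variance, with linear rise and retention at 9/12 months ranged from 0.70/0.70 to 0.60/0.50, power is 98–99% if kept, 73–75% if half is lost and 13–21% if all is lost; the late effect is rejected 77–89% of the time. Even in the linear, sustained case the line fitted over six visits implies a 6-month difference of only 10.6–10.9, not 16.

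**4. Tests at the 6-month horizon, N = 190.** Interaction on baseline, 10 weeks and 6 months, linear rise, variance 504/0.92: slope 2.667, power 0.81. Single 6-month contrast, variance 504: SE = √(4 × 504/(190 × 0.70)) = 3.89, 16/3.89 = 4.11, power 0.97. Neither uses data after 6 months in these calculations.

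**The case against.** The strongest defence is that one longitudinal model over all visits, with 6 months primary and later comparisons secondary, is ordinary practice. The article says the 9- and 12-month comparisons are made within longitudinal analyses. It also allows categorical time, from which a 6-month contrast follows directly, and naming that contrast is often left to an analysis plan. This softens the conflict. It does not remove it: continuous time comes first, the interaction is what matters, and a joint interaction test on categorical visits would still draw on 9 and 12 months.

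Some stronger readings are not supported:

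- A reader might infer that the entry rule (at least 20% of doses missed) biases the test through regression to the mean. That selection precedes randomization and affects both arms alike, so in expectation it cancels from the treatment-by-time term.
- A reader might infer that the change-from-baseline model is the adopted primary analysis, so that baseline can never be a response. The article adopts it for the power calculation and only considers it for the analysis.
- A reader might infer that the six-visit slope test is simply weaker. If the effect is sustained it is not: 0.98–0.99 against 0.97 for the 6-month contrast.
- That screening TRQ enters the model is inferred from the list of assessments. The schedule in Table 2 is not shown.

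**Conclusion.** The point holds as an internal conflict over which horizon decides Aim 2. Taken as written, the primary slope test can succeed or fail on data that the plan calls secondary, with the 6-month effect unchanged. Power ranges from about 0.98–0.99 down to 0.09–0.18 according to what happens after 6 months, and a purely late effect is called significant about 0.87 of the time.

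The sizes rest on assumed trajectories and on retention after 6 months, neither of which the article gives. Ranging later retention and the reading of 504 moves the figures but not the conclusion. The matter should be settled before analysis because it determines the primary test.

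**What to change.** State that the primary Aim 2 test is at the 6-month horizon, in one of two ways:

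- **Limit the treatment-by-time interaction to data through 6 months** (baseline, 10 weeks, 6 months), with TRQ itself as the response. This matches the stated 182 and gives about 81% power at 190.
- **Fit visit as categorical with baseline TRQ as a covariate and name the 6-month CAE–eTAU contrast as primary.** This replaces the interaction that was powered, so the power basis must be restated. On the plan's inputs a two-group comparison at 6 months needs 2 × 9.505 × 504/256 = 37.4, so 38 per arm, then 38/0.70, so 55 per arm or 110 in total. The 0.97 power at 190 does not carry over to an unadjusted change score: its variance is 2 × 504 × 0.92 = 927, SE = √(4 × 927/133) = 5.28, and power is about 0.78.

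In either case keep the 9- and 12-month comparisons secondary and do not use screening TRQ as a response. If difference values from baseline are analysed, say that only the four post-baseline visits are responses, and do not test a slope across them. A benefit complete by 10 weeks and then sustained has zero slope there and would be detected only at the 0.025 error rate.

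Cost: no change to sample size, visits or data collection. It is more than an edit of wording, because the second option changes the primary test. The primary test becomes more narrowly defined, persistence after 6 months becomes a secondary question, and the power statement may need rewording.
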